#### Primary outcome

The primary outcome is the physical component of the SF-36 quality of life questionnaire measured in ICU survivors at 6 months. Based on the study by Kayambu et al. [12], where this measure was 60 ± 29 points in the control group, our study is powered to detect a change by 15 points or more, which is within the limits determined as clinically important for patients with COPD, asthma and myocardial infarction [56]. The SF-36 has been validated in the Czech Republic and endorsed by the Institution for Health Information and Statistics (https://www.uzis.cz/en/node/8159).

#### Secondary outcomes

Four-item Physical Fitness in Intensive Care Test (time frame: at 28 days or discharge from the ICU, whichever occurs earlier) as the functional outcome at ICU D/CMuscle mass measured by rectus muscle cross-sectional area on B-mode ultrasound (time frame: at 7-day intervals up to day 28 or discharge from the ICU, whichever occurs earlier)Nitrogen balance measured in grams per metre-squared of body surface area (time frame: at 7-day intervals up to day 28 day or discharge from the ICU, whichever occurs earlier) and the cumulative the difference between nitrogen intake and outputMuscle power as per the Medical Research Council (MRC) score (time frame: at 7-day intervals up to day 28 or discharge from the ICU, whichever occurs earlier)Number of ventilator-free days (time frame: at 28 days); that is, number of days, out of 28 days after admission, that the patient has NOT been supported by mechanical ventilationNumber of rehabilitation interruptions due to physiological deterioration (time frame: at 28 days or discharge from the ICU, whichever occurs earlier)Number of episodes of elevated intracranial pressure (time frame: at 28 days or discharge from the ICU, whichever occurs earlier)Number of dialysis interruptions (time frame: at 28 days or discharge from the ICU, whichever occurs earlier)Length of ICU stay in days (time frame: at 6 months)

### Study population

One hundred and fifty participants meeting the eligibility criteria will be recruited in four ICUs at FNKV University Hospital.

Inclusion criteria: age ≥ 18 years; mechanical ventilation, or imminent need of it at presentation; predicted ICU length of stay ≥ 7 days.

Exclusion criteria: known primary systemic neuromuscular disease or spinal cord lesion at admission; severe lower limb injury or amputation; bedridden premorbid state (Charleston Comorbidity Score > 4); approaching imminent death or withdrawal of medical treatment within 24 h; pregnancy; presence of external fixator or superficial metallic implants in lower limbs; open wounds or skin abrasions at electrode application points; presence of pacemaker, implanted defibrillator, or other implanted electronic medical device; predicted as unable to receive first rehabilitation session within 72 h of admission or transferred from another ICU after more than 24 h of mechanical ventilation; presence of other condition preventing the use of FES-CE or considered unsuitable for the study by a responsible medical team; prior participation in another functional outcome-based intervention research study.

With the exception that we do not limit the study population with sepsis, we have intentionally chosen similar criteria to the only study underway on FES-CE in ICU patients, which is primarily focused on muscle structure and function [57].

### Interventions

The flow of participants throughout the trial is shown in Fig. 1 and the study procedures in Fig. 2. As soon as informed consent has been obtained, and prior to randomization, baseline testing including anthropometric examination will be performed. In addition, in patients with specific consent, a muscle biopsy will be obtained and hyperinsulinaemic clamp will be performed on the first morning (8.00–11.00 a.m.) and prior to the start of enteral nutrition.

**Fig. 1 Fig1:**
[figure not shown]
Planned flowchart of patients enrolled into the trial. D7 day 7, D/C discharge, FES-CE functional electrical stimulation-assisted cycle ergometry, ICU intensive care unit, tx treatment, NMS neuromuscular stimulation, PCBE passive cycling-based exercise

**Fig. 2 Fig2:**
[figure not shown]
Standard Protocol Items: Recommendations for Interventional Trials (SPIRIT) figure. D day, D/C discharge, EGDR early goal-directed rehabilitation, F-up follow-up, ICU intensive care unit, MRC Medical Research Council, MV mechanical ventilation, RHB rehabilitation, SF-36 Short Form 36, SOFA Sequential Organ Failure Assessment, CCS Charlson comorbidity score, ROM range of motion, PFIT physical function test for use in the intensive care unit

#### Standard care group

Both groups will receive usual best medical and nursing care in the ICU, which includes daily sedation holds when applicable and delirium 12-hourly monitoring (by CAM-ICU scale [58]) and management as usual in the routine practice. Respiratory physiotherapy will also be delivered without alterations. The routine standard care arm will undergo mobilization/rehabilitation delivered by personnel not involved in the study in a usual, routine way. Details of physiotherapy treatment will be recorded but not protocolled in the standard care arm.

#### Intervention group

In the intervention arm, early goal-directed rehabilitation is protocolled according to the patients’ condition and degree of cooperation (Fig. 3), and there will be pre-defined safety criteria, which are in accordance with current recommendations for active rehabilitation of critically ill ventilated adults [13]. Whilst the safety criteria are binding for the study physiotherapist, the rehabilitation protocol is not and the delivery of physical exercise can be altered according to the actual patient’s condition. However, any alteration and the reason for it will be recorded. The intervention will start as soon as possible and always within 72 h of ICU admission, continuing until ICU discharge. Supine cycling will be delivered as per protocol on a supine cycle ergometer attached to a neuromuscular stimulator. Surface electrodes will be applied to the gluteal, hamstring and quadriceps muscles on both legs. The intensity of muscle stimulation will be delivered at a level able to cause visible contractions (confirmed by palpation if uncertain) in all muscle groups without causing undue pain or discomfort to the participant, according to a regime specified by Parry et al. [44]. Once the patient is more alert, and able to participate, they will be provided with standardized encouragement to engage in therapy. To increase the intervention workload, resistance will be increased incrementally and cycling cadence. If a participant is readmitted to intensive care, the intervention will be re-initiated. The intervention continues until day 28 or ICU discharge, whichever occurs earlier.

**Fig. 3 Fig3:**
[figure not shown]
Protocol of intensified goal-directed rehabilitation. FES-CE functional electrical stimulation-assisted cycle ergometry, FIO_2_ fraction of inspired oxygen, LL lower limb, RASS Richmond Agitation and Sedation Scale, UL upper limb

## Methods

### Enrolment and randomization

All patients admitted to participating ICUs are screened daily by research nurses and all eligible patients or their representatives are approached by investigators as soon as possible, but always within 72 h of admission. Participants for whom informed consent was obtained will be randomly assigned (1:1) to receive either standard care or the intervention using offsite independent randomization protocols (www.randomization.com) embedded in the electronic case report form. Randomization will be stratified according to the presence or absence of sepsis and the availability of a biopsy at baseline. There is no restriction (blocking) during randomization.

Both the study team and clinical personnel will be made aware of subject treatment allocation. The outcome assessor is not involved in patient care and remains blinded to treatment allocations.

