### Statistical analyses

#### Sample-size calculation

In studies of critical illness outcome at 6 months using SF-36 scores, the standard deviation varied between 10 and 30 points. In order to have 80% power to detect a 15-point difference in SF-36 scores between control and intervention at the level of significance *p* < 0.05 in the population with a mean of 60 and SD of 30 [12], we would need 108 subjects (54 in each arm). In order to allow for deaths and dropouts, we plan to randomize 150 subjects.

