#### Data analysis plan

The primary outcome and all secondary outcomes will be compared between the intervention and standard of care groups in an intention-to-treat population, with all tests two-sided and with the level of significance set at 5%, after the primary outcome has been collected in the last subject. There is no plan for any interim analysis. We will perform exploratory analyses in pre-specified subgroups of patients stratified according to APACHE II, and the length of intervention. We will also perform unadjusted analysis of odds ratio of being functionally independent (defined as ability to walk, use a telephone, self-care, use the toilet and groom) at 6 months after ICU admission in patients in the intervention and standard of care groups. We will perform adjustments on the disease severity (APACHE II score), admission diagnosis, baseline functional status and age. Missing data for primary outcome will be dealt by reporting both worst-case and per-protocol results; no imputation will be used.

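### Randomisation is described as stratified yet unrestricted, so the stratification balances nothing, and the adjustment list names neither stratification factor nor the outcome it serves

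*Protocol article*

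**What the plan says.** Under Enrolment and randomization, the Protocol article says that consented participants "will be randomly assigned (1:1) to receive either standard care or the intervention". It continues: "Randomization will be stratified according to the presence or absence of sepsis and the availability of a biopsy at baseline". The next sentence reads: "There is no restriction (blocking) during randomization". No minimisation, urn scheme or other balancing device is mentioned.

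The Data analysis plan opens by stating that "The primary outcome and all secondary outcomes will be compared between the intervention and standard of care groups in an intention-to-treat population"; no model or covariate is given for that comparison. Later in the same paragraph comes a secondary analysis: "We will also perform unadjusted analysis of odds ratio of being functionally independent". Directly after it stands the adjustment sentence: "We will perform adjustments on the disease severity (APACHE II score), admission diagnosis, baseline functional status and age". That sentence names no outcome, and neither sepsis nor biopsy availability is on its list.

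**The concern.** Stratification balances arms only if allocation is constrained within each stratum, by blocks or an equivalent device. If allocation is stratified but unconstrained, the separate lists have no effect on balance. Either the stratification is inoperative or the sentence on restriction is wrong, and the article does not let the reader tell which.

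The sponsor thought sepsis and biopsy availability important enough to stratify on. As written, neither is balanced by design or named for adjustment. At stake are chance imbalance in sepsis across the trial, uneven arms in the small biopsy and clamp subgroup on which the third hypothesis rests, and some precision in the primary comparison.

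**Working it through.** **Inputs.** From the article: 1:1 allocation; two binary factors, hence four strata; no restriction; 150 randomised; 108 evaluable (54 per arm); 15-point difference; SD 30; two-sided 5%; biopsy subgroup of 30. Assumed, because the article gives no figure: sepsis prevalence of 30%, 50% or 70%, and share of outcome variance explained by covariates (R²) of 10–30%.

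**The plan's own figure.** n per arm = 2 × (30/15)² × (1.960 + 0.842)² = 62.8, so 63, not 54. With 54 per arm, power is 73.8% by the normal approximation and 73.1% by the t-test. This discrepancy is a separate matter and is used below only as a starting point for precision.

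**Equivalence.** With independent fair draws, any given sequence of 150 allocations has probability (1/2)^150, whether the draws come from one list or four. A simulation (20,000 replicates, 150 patients, 30 with biopsy) agrees. The entries are the chance that sepsis prevalence differs between arms by 10 points or more:

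| Assumed prevalence | Stratified, unrestricted | Unstratified | Stratified, blocks of 4 (illustration) |
|---|---|---|---|
| 30% | 18.7% | 18.5% | about 0 |
| 50% | 22.1% | 22.0% | about 0 |
| 70% | 18.2% | 18.1% | about 0 |

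A hand check at 50%: the SD of the difference is √(0.25 × 2/75) = 0.082, so 10 points is 1.22 SDs, a two-sided chance of 22%.

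**Biopsy subgroup.** With X ~ Binomial(30, 0.5):
- 18:12 or worse: 2·P(X ≥ 18) = 36.2%
- 19:11 or worse: 2·P(X ≥ 19) = 20.0%
- 20:10 or worse: 2·P(X ≥ 20) = 9.9%

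**What uneven numbers cost.** The variance of a mean difference is proportional to 1/n₁ + 1/n₂.
- 18:12 gives 0.139 against 2/15 = 0.133 for 15:15: variance up about 4%, standard error up about 2%.
- 20:10 gives 0.150: variance up 12.5%, standard error up about 6%.
- In the main trial, a difference in arm size of 20 or more out of 150 has a 12.0% chance. For the primary comparison, 44/64 instead of 54/54 lowers power from 73.8% to 72.3% (normal approximation).

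**What adjustment could gain.** Residual SD = 30 × √(1 − R²); t-test power at 54 per arm for 15 points:

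| R² (assumed) | Residual SD | Power |
|---|---|---|
| 0 | 30.0 | 73.1% |
| 10% | 28.5 | 77.5% |
| 15% | 27.7 | 79.7% |
| 30% | 25.1 | 86.8% |

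**The case against.** The strongest reply has four parts.

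*The model belongs in the analysis plan.* A condensed article may leave the primary model to a statistical analysis plan, which was not available here. That stands: the absence of a model is no fault in itself. But the article does publish a covariate list, and that list omits both of its own stratification factors and is attached to no outcome.

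*The adjustments may already cover the primary outcome.* A reader might infer from their position that they apply only to the functional-independence odds ratio. The text does not establish this. The paragraph begins with the primary and secondary outcomes, and the preceding analysis is explicitly unadjusted, so the sentence can equally be read as general. It is ambiguous. On the general reading, much of the precision gain above is already planned.

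*Sepsis may be covered in part.* Admission diagnosis is listed and may capture some of it, so it would be too strong to say that sepsis is ignored. The article does not say that it does, and nothing listed captures biopsy availability.

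*Simple randomisation is legitimate.* It creates no design-based obligation to adjust for these factors, and avoiding blocks is defensible in a single-centre trial whose study team and clinical staff know allocations. Both points stand. The case for adjustment then rests on prognostic value, for which the article gives no estimate. Neither point reconciles the two sentences on allocation.

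**Conclusion.** The point holds as a description that is wrong as written, together with an adjustment list that is incomplete and unattached. As described, allocation is equivalent to simple randomisation. The chance of a 10-point sepsis imbalance is about 18–22% (assumed prevalence 30–70%), and the chance of a 20:10 or worse biopsy split is 9.9%.

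A reader might infer that the trial's test is biased or its error rate inflated. The documents do not support that. Under simple randomisation the unadjusted test is valid; if allocation was in fact restricted, ignoring the factors tends to be conservative. Uneven arm sizes alone cost little. Nor should the roughly 73% power be charged to this point, since it comes from the sample-size calculation. The consequence is uncorrected chance imbalance and possibly some lost precision, the latter depending wholly on the assumed R² and on whether the listed adjustments already apply to the SF-36 comparison.

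**What to change.** 1. In Enrolment and randomization, describe the method actually used: either call it simple randomisation, or state the restriction applied within strata and remove the sentence denying one.
2. Before unblinded analysis, state that the primary 6-month SF-36 comparison is a linear model on arm, sepsis and biopsy stratum plus the four covariates already listed (APACHE II, admission diagnosis, baseline functional status, age).
3. Adjust the secondary comparisons for sepsis and biopsy stratum. Adjust the biopsy-subgroup comparisons for sepsis only, because biopsy status is constant there.
4. Permuted blocks are optional and matter only for allocations still to come. The Trial status section expected recruitment to finish in November 2019, so few or none may remain. If used, block sizes should vary and be concealed, since blocks are somewhat predictable when staff know allocations.

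Items 1 to 3 cost wording only. The stratification factors and the listed covariates are baseline data that the plan already relies on.

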### Clinical data retrieval and handling

The ICUs are paperless and fully computerized, so vital functions and other physiological parameters are monitored and data are routinely stored in secure hospital data bases via a protected dedicated network (MetaVision; IMD Soft Inc.). This includes data about nutritional intake and urinary output. On top of this, research nurses will input data into an electronic, secure, customized online case report form database (eCRF; accessible at https://195.113.79.251:9090/apex/f?p=103:101:14992036032980). Data protection and encryption is in accordance with the EU’s General Data Protection Regulations as well as Czech data protection laws. The data will be audited by on a regular basis, but at least after each 10 patients are enrolled, by independent study monitor. After the database is locked upon study completion, patients’ data will be de-identified and available in full in a public database.

### Complementary studies: insulin resistance and mitochondrial function

These studies will be performed in addition to other study procedures in a nested subgroup of patients, who give specific consent. The first measurement will be performed at baseline prior to randomization, ideally the next morning after admission. Second measurement will be performed on day 7 of ICU stay, i.e. after at least 5 days of intervention.

#### Muscle biopsy

Muscle biopsy will be performed from the vastus lateralis muscle using the Bergstrom needle biopsy technique. The sample will be separated into three parts (50–100 mg each). One part will be immediately frozen in liquid nitrogen for analysis of the protein/DNA ratio and for protein expression studies. The second part will be frozen in liquid nitrogen-cooled isopentone for muscle fibre typing and immunohistochemistry analysis. The third part put will be placed in BIOPS media on ice for the preparation of homogenates and measurement of citrate synthase activity, spectrophotometric analysis of the activity of respiratory complexes I–IV [52] and western blot analysis of respiratory complexes (as described in [55]). In the fresh muscle homogenates, we will use high-resolution respirometry (Oxygraph; Oroboros, Austria) to determine the function of individual respiratory complexes in the cytosolic context and measure basic functional metabolic indices by a method we have recently developed and calibrated against isolated mitochondria [59]. We will specifically look at the degree of mitochondrial uncoupling, the respiratory chain capacity and the function of individual complexes, including glycerol-3-phosphate shuttle. From the satellite cells we will prepare a culture of myotubes, which will serve as an in vitro model of skeletal muscle [60] and specifically measure the in vitro ability of myotubes to oxidize fatty acids by extracellular flux analysis (Seahorse Biosciences). Frozen muscle samples will be stored at − 80 °C for analysis of the DNA/protein ratio, mRNA and proteins involved in the regulation of proteolysis, substrate oxidation and anabolic pathways of skeletal muscle (MuRF, FOXO, atrogins) as well as immunohistochemistry and typing of muscle fibres. In order to determine which changes are caused by critical illness itself, we will also obtain control samples (*n* = 15) from age, sex and BMI-matched metabolically healthy volunteers undergoing elective hip surgery at the Department of Orthopaedic Surgery. In addition, we will look at the change of these indices after 7 days of critical illness and the influence of the intervention versus standard of care. We will look at correlation of these parameters with muscle power (i.e. compare the bioenergetics profile of skeletal muscle in those who develop ICUAW and in those who do not) and insulin resistance.

*Insulin sensitivity* and substrate oxidation will be measured after overnight fasting by hyperinsulinaemic euglycemic clamp (as described in [61]). We will compare the effect of intervention on insulin-mediated glucose disposal.

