**Methods:**

An assessor-blinded, pragmatic, single-centre randomized controlled trial will be performed. Adults (*n* = 150) mechanically ventilated for < 48 h from four ICUs who are estimated to need > 7 days of critical care will be randomized (1:1) to receive either standard of care or FES-CE-based intensified rehabilitation, which will continue until ICU discharge. Primary outcome: quality of life measured by 36-Item Short Form Health Survey score at 6 months. Secondary outcomes: functional performance at ICU discharge, muscle mass (vastus ultrasound, N-balance) and function (Medical Research Council score, insulin sensitivity). In a subgroup (*n* = 30) we will assess insulin sensitivity and perform skeletal muscle biopsies to look at mitochondrial function, fibre typing and regulatory protein expression.

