### Objectives

To investigate, in a pragmatic, prospective, randomized, controlled, assessor-blinded trial, the effects of very early intensive rehabilitation using a goal-directed protocol that includes FES-CE in mechanically ventilated ICU patients predicted to need a protracted ICU stayTo perform more detailed metabolic studies, including serial muscle biopsies and using euglycaemic hyperinsulinaemic clamps, in a nested subgroup. Insulin sensitivity in the whole study population will be compared by glucose control and consumption of intravenous insulin required to control blood glucose

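### Minor, ancillary sub-study only: biopsy controls must be metabolically healthy but nested patients need not be, so prior diabetes can contribute to a difference the plan attributes to critical illness

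*Protocol article*

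**What the plan says.** The Muscle biopsy section states the aim of the control comparison in causal terms: "In order to determine which changes are caused by critical illness itself, we will also obtain control samples". The controls are 15 "age, sex and BMI-matched metabolically healthy volunteers undergoing elective hip surgery".

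The abstract puts the patient side at 30: "In a subgroup (*n* = 30) we will assess insulin sensitivity and perform skeletal muscle biopsies". Entry is described under Complementary studies: "These studies will be performed in addition to other study procedures in a nested subgroup of patients, who give specific consent". Ethical considerations likewise describes a second tier of consent and adds no metabolic condition; it only keeps patients enrolled on an independent physician's assent out of the clamps and biopsies.

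The trial's inclusion criteria are "age ≥ 18 years; mechanical ventilation, or imminent need of it at presentation; predicted ICU length of stay ≥ 7 days". The exclusions under Study population do not name diabetes, insulin treatment or other metabolic disease. The only comorbidity threshold is attached to a bedridden state before admission, and there is a general discretion to leave out patients judged unsuitable.

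A second, separate statement stands under Objectives: "Insulin sensitivity in the whole study population will be compared by glucose control and consumption of intravenous insulin required to control blood glucose". Prior diabetes is neither a stratification factor (these are sepsis and availability of a baseline biopsy) nor among the adjustment factors in the Data analysis plan (APACHE II, admission diagnosis, baseline functional status, age).

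**The concern.** A metabolic-health condition is set on one side of the comparison only. As written, patients and controls may differ in critical illness and also in metabolic disease that existed before it. Matching on age, sex and BMI does not remove that second difference.

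The article's own rationale makes this relevant. It builds the case for the sub-study on insulin resistance, failed glucose transport and mitochondrial dysfunction in muscle, and it plans to correlate the biopsy indices with insulin resistance. Diabetes before admission plausibly bears on the same constructs. At stake is one interpretation: how much of a patient-control difference in the biopsy indices may be credited to critical illness.

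**Working it through.** The article gives no calculation for the 30 patients or the 15 controls, so there is no figure to reproduce. The check sets the entry rules side by side and then shows how large the effect could be.

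**Entry rules**

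| | Nested patients | Controls |
|---|---|---|
| Number | 30 | 15 |
| Entry | Trial eligibility plus specific consent | Elective hip surgery |
| Metabolic condition | None stated | Must be metabolically healthy |
| Matching | – | Age, sex, BMI |

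**Size of the possible bias.** Let p be the share of nested patients with diabetes before admission and d the shift diabetes causes in an index, in SD units. Controls have a share of zero, so

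bias = p × d − 0 × d = p × d.

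Both p and d are assumptions. Further assumptions are that all 30 patients contribute a sample, that the two groups are analysed as independent, and that the SD is 1 within patients without diabetes and within controls.

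Without any shift, SE = √(1/30 + 1/15) = 0.316 SD. The difference detectable with 80% power at two-sided 5% is (1.960 + 0.842) × 0.316 = 0.89 SD.

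With a shift, the patient variance becomes 1 + p(1 − p)d². If critical illness had no effect on the index, the chance of a significant result is Φ(b/s − 1.96) + Φ(−b/s − 1.96), with b = p × d and s = √([1 + p(1 − p)d²]/30 + 1/15). For p = 20% and d = 1.0: b = 0.20, s = √(1.16/30 + 1/15) = 0.325, b/s = 0.62, and the result is 9.5%.

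| p (patients of 30) | d = 0.5 | d = 1.0 | d = 1.5 |
|---|---|---|---|
| 10% (3) | 0.05 SD; 5.3% | 0.10 SD; 6.1% | 0.15 SD; 7.4% |
| 20% (6) | 0.10 SD; 6.1% | 0.20 SD; 9.5% | 0.30 SD; 14.6% |
| 30% (9) | 0.15 SD; 7.6% | 0.30 SD; 15.1% | 0.45 SD; 26.2% |

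Each cell gives the bias and the false-positive rate; the nominal rate is 5%. A larger sample would not shrink the bias. Even at p = 10%, the chance of at least one patient with diabetes among 30 is 1 − 0.9³⁰ = 96%.

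**Cost of restricting the contrast.** With k patients left, the detectable difference is 2.802 × √(1/k + 1/15):

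- k = 27 (10% excluded): 0.90 SD
- k = 24 (20% excluded): 0.92 SD
- k = 21 (30% excluded): 0.95 SD

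**The case against.** The strongest reply is that this rests on silence in a condensed article. The full protocol is not shown and could hold a sub-study entry rule or a definition of metabolic health, and the discretionary exclusion could remove some patients. This stands in part: the article does not say that patients with diabetes are enrolled, only that nothing listed keeps them out. But it does state the eligibility list, the control definition and the causal purpose, and these three do not fit together as they stand. A case-by-case discretion is not a metabolic criterion.

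It is also fair that the contrast is ancillary. The three hypotheses all compare intervention with standard of care, and the control comparison is in no listed primary or secondary outcome. The controls are described as giving muscle samples only, so nothing shows that clamp results are compared with them.

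A reader might go further and infer that an uneven split of diabetes between two small arms biases the randomised comparison of insulin sensitivity. The documents do not support that. Chance imbalance under randomisation is not bias. Clamp and biopsy are also done before randomisation and repeated on day 7, so each patient's prior state is measured. Nor does an argument about small nested arms carry over to intravenous insulin consumption, which is compared across the whole trial, planned at 150.

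**Conclusion.** The point holds as a cheap improvement of minor weight, confined to the patient-versus-control contrast in the biopsy sub-study. The plan as written leaves that contrast open to confounding by prior metabolic disease, so its causal wording claims more than the design supports.

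The size cannot be determined from the article. It is p × d, and over the assumed ranges it goes from 0.05 SD with an almost nominal error rate to 0.45 SD with a false-positive rate of 26.2%. The error rates assume no true effect of critical illness on the index; where there is a true effect, the same p × d distorts its estimated size instead.

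The comparisons between randomised arms, the within-patient change to day 7 and the SF-36 outcome do not use the controls and are untouched. For intravenous insulin consumption, the absence of prior diabetes from the named factors is at most a missed gain in precision.

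**What to change.** For the patient-versus-control contrast:

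- Add an analysis restricted to patients without known diabetes or glucose-lowering treatment before admission, and show it beside the all-patient result.
- Check that the age, sex and BMI matching still holds after the restriction.
- Limit the causal wording to what the restricted analysis supports, since undiagnosed disease may remain and the article does not define metabolic health.

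Separately, for precision and not as a correction of bias:

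- Include known diabetes before admission as a covariate when intravenous insulin consumption is compared between arms in the whole trial.
- Analyse clamp insulin sensitivity adjusted for its own pre-randomisation value.

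No new study procedure is needed. The article does not say whether prior diabetes and its treatment are recorded; if they are not, this is an item of medical history to add. The statistical cost is a smaller patient group in the restricted contrast, about 21 to 27 of 30 if 10-30% have diabetes (an assumption), with the small loss of precision shown above.
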